### Inclusion criteria

Adolescents will be deemed eligible for participation if they satisfy the following criteria.
i.Between the ages of 10 and 19 years.ii.Present at any of the selected health facilities for delivery, antenatal care within their third trimester or post-natal care within two weeks of delivery.iii.Consent to participate in the study.

Eligibility criteria for health professionals are.
i.Health providers including midwives and administrators who are in full time employment at the selected health facilities.ii.Consent to participate in the study.

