### Sampling procedure

Multistage, stratified and systematic sampling will be used to recruit study participants from the facilities where they attend. Using data available from the 2010 Population and Housing Census, three out of the formerly ten regions in Ghana with adolescent pregnancy rates higher than the national average (14%) were randomly selected. Subsequently, six districts were purposefully selected from these regions considering appropriateness for the intervention, available resources, and geographical non-proximity between intervention and control facilities. Facilities in the intervention and control arms of the study were matched based on the number of adolescent pregnancies delivered annually using the Ghana Health Service District Health Information Management System (GHS-DHIMS) data from 2018 as a guide.

All eligible adolescent participants who attend the participating intervention and control facilities for antenatal care in their third trimester and delivery will be invited to enrol in the study by a trained research assistant. The nature of the study and all ethical concerns will be explained to the candidate prior to their enrolment. Enrolment will be run on a cumulative bases until the minimum sample size is satisfied. Some adolescents will be purposively selected to participate in the adolescent IDIs based on their characteristics which is aimed at achieving maximum variability of participants. Each district will have a health professional who works in administrative capacity and in a caregiving capacity invited to participate in the Key Informant Interviews.

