### Data collection procedure

The quantitative interviews will be administered by trained research assistants. Interviews will be administered both at baseline and endline (from day 1 following the intervention). They are estimated to last between 30 and 45 min per participant and will be held at the home of the participant or a convenient private venue outside the health facility within two weeks after delivery. This venue arrangement is considered important to create an enabling environment which allows free and candid dialogue with the participant which may not be possible at the health facility due to fear of retaliation from providers. This time interval between delivery and the interview is also considered adequate for the parturient to recuperate without introducing significant recall bias. Interviews with adolescent participants will be in the most commonly spoken languages in the district which are English, Twi, Dangme or Krobo, based on the preference of the participant. This will allow the participants to express themselves freely in the language they are most comfortable with.

Qualitative IDIs will be conducted with selected adolescent participants and KIIs with health professionals. Interviews will be audio-taped, with prior permission from the participant. Additionally, notes will be taken to capture non-verbal nuances and expressions which may aid in better analysis and interpretation of the audio information. The number of interviews will continue until a saturation of information is reached. Each interview is estimated to last between 45 and 60 min. For adolescents, IDIs will take place at a location convenient to the participant outside the facility within two weeks after delivery. Similar to the quantitative interviews, the qualitative interviews will be conducted within a post-recovery timeframe which mitigates the probability of recall bias. Based on the preference of the participant, IDIs will be conducted in English, Twi, Ga-Dangme or Krobo as done in the quantitative interviews. The KIIs will be conducted within the facilities where the staff work and will be conducted in English.

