Sex: femaleAge: 18 to 25 yearsAcademic qualification: minimum of a secondary school certificateTechnical proficiency: smartphone literacyLanguage proficiency: at least one of the languages (Ga-Dangme/ Krobo/Twi)The age group and sex of the assistants will help establish rapport between the assistants and participants. This will also help minimize response desirability bias on the side of participants. The educational and technical criterion are necessary to ensure that the assistants understand and effectively carry out their roles in the study to collect quality data. The assistants will undergo a two-day training on the theoretical background of the study, enrolment and obtaining consent from participants, administration of questionnaires and facilitation of interviews, as well as ethical issues. The principal investigator will always closely supervise the research assistants to ensure their observance of study protocols and ethical codesData Collection Instruments: The data collection instruments are adapted from a previous multi-country study (which included Ghana) which included parturient women of all ages [46] instruments will be adapted for use with adolescents. The tools will be pretested on 5% of the sample size in a pilot facility in the Kpone-Katamanso district and modified accordingly based on findings from the pilot. The pilot district was selected based on its similarity to study sites in having an adolescent birth rate of greater than 11%.Data Collection Timing and Location: Data collection at baseline will be over a 3-month period. Endline data collection will start from day 1 after the intervention until three-months post-intervention. The venue and time interval between delivery and the adolescent surveys will allow participants express themselves freely without fear of victimization by health providers. This will also allow the participants enough recovery time from childbirth with minimal recall bias.Data Monitoring: Data collection will be conducted in real time electronically. The data will be monitored daily to allow early detection of discrepancies and resultant remedial action. Transcripts from audio interviews will be reviewed by an independent listener who is fluent in the language and did not conduct or transcribe the interview to audit for accuracy and completeness.

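### Endline opens by interview date on the day after training, so births from up to two weeks earlier, before the training, can be counted as post-training

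*Protocol article*

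**What the plan says.** The timing rule appears twice in the protocol article. Data collection procedure states: "Interviews will be administered both at baseline and endline (from day 1 following the intervention". Data quality assurance activities repeats it: "Endline data collection will start from day 1 after the intervention until three-months post-intervention". For the pre-test wave it gives only a length: "Data collection at baseline will be over a 3-month period".

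Data collection procedure also fixes the interval between birth and interview. Interviews "will be held at the home of the participant or a convenient private venue outside the health facility within two weeks after delivery", and this interval is justified as time for the adolescent to recuperate.

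Entry to the study is described in two ways. Inclusion criteria admit adolescents present for delivery, "antenatal care within their third trimester or post-natal care within two weeks of delivery", with no earliest date of delivery. Sampling procedure describes invitation of those attending for "antenatal care in their third trimester and delivery will be invited to enrol in the study by a trained research assistant" and does not name post-natal attenders. It adds: "Enrolment will be run on a cumulative bases until the minimum sample size is satisfied".

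Data processing and statistical analysis defines the primary outcome as disrespectful care during labour and uses DID for the training effect. Intervention states that nothing is done in the control facilities.

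**The concern.** The outcome happens at the birth and the interview only reports it. Whether a birth could have been attended by trained midwives depends on when it took place relative to the training. The stated rule attaches the start of endline to the interview instead, and the interview may follow the birth by up to 14 days.

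The two rules meet badly in the first fortnight. An adolescent interviewed at home on day 1, after some time to recuperate, will in practice have delivered before or during the training. The post-natal entry route lets such adolescents into the study, and no sentence requires an endline birth to follow the training.

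The error runs in one direction. In the intervention arm, endline would mix untrained with trained attendance. In the control arm no midwife is trained at either time, so nothing is misclassified there in this sense. The result is bias towards no effect in the main contrast, and a larger sample would not remove it.

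A smaller gap goes with this. The boundary is defined by the intervention, which has no date in a control facility, so the start of endline there is not fixed by the text.

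**Working it through.** The plan states no figure for this share, so there is none to reproduce. The calculation gives the size of the problem under stated assumptions.

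**Inputs from the protocol article**
- Endline window W: three months, taken as 91 days.
- Lag L from birth to interview: 0 to 14 days.
- Prevalence without training 0.18, and an absolute reduction of 0.10, so 0.08 with training (Sample size determination).

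**Assumptions, not in the article**
- Constant birth rate, with interviews spread evenly over the window.
- Lag distribution: either even over 0 to 14 days (mean 7), or all near day 14 as the extreme.
- No change over time in the control arm, and the full effect for every birth after training.

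**Share of endline births that preceded training.** An interview t days after training concerns an earlier birth when L > t. With t uniform on 0 to W and L never longer than W, the share is f = mean(L)/W.
- Even lags: f = 7/91 = 7.7%.
- All near day 14: f = 14/91 = 15.4%.
- Endline enrolment begins only after training, among antenatal and delivery attenders: f is near 0%.

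**Effect that would be seen.** Endline prevalence in the intervention arm is 0.18f + 0.08(1 − f), so the apparent reduction is 10 × (1 − f) points.
- f = 0.077: 10 × 0.923 = 9.2 points.
- f = 0.154: 10 × 0.846 = 8.5 points.

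**If enrolment fills early.** The share varies as 1/W. A 60-day window, assumed only for illustration, gives 7/60 = 11.7% with even lags. The article does not say how long enrolment will take.

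**Rough consequence for power.** The article's formula gives 2 × (1.96 + 0.842)²/0.1² × 0.13 × 0.87 = 177.6, or 178 per arm before adjustments. For a simple two-group endline comparison with 178 per arm and a 90-day window:

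| Case | Share | Apparent reduction | Power |
|---|---|---|---|
| No misplaced births | 0% | 10.0 points | 80% |
| Even lags | 7/90 = 7.8% | 9.2 points | about 73% |
| All near day 14 | 14/90 = 15.6% | 8.4 points | about 64% |

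These powers ignore the extra variance of a DID contrast. They show direction and rough size only. The point does not depend on how the stated total of 392 was reached.

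**The case against.** The best reply is that recruitment in practice follows Sampling procedure, which invites adolescents at third-trimester antenatal care and at delivery. Data collection could be read to include enrolment. If endline enrolment through that route opens on day 1, almost every endline birth follows the training and the problem all but vanishes. This is why the range must start near 0%. It does not settle the matter: the text ties day 1 to the interviews, and Inclusion criteria admit adolescents who have already delivered.

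A second reply is that an article leaves the handling of transition births to the full protocol. That would answer a complaint about missing detail. Here a rule is stated, in two places, and followed literally it puts births in the wrong wave.

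A third reply is that the date of delivery must be known anyway for the two-week rule, so early endline births could be moved or dropped at analysis. This is true and limits the harm. But enrolment stops when the target is met, so places taken by births before training would leave endline short after they are dropped.

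It is also fair that over the full three months with even lags the loss is less than one percentage point.

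**Conclusion.** The point holds and is modest. As written, about 0% to 8% of intervention-arm endline births over three months could precede the training, and 15% if all interviews fall near day 14. A true 10-point reduction would then show as 10 down to 9.2 points, or 8.5 at the extreme. These figures rest on an assumed lag distribution, a constant birth rate and a full 91-day window. The share is larger if enrolment fills early.

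Three stronger readings are tempting, and the documents do not support them.
- A reader might infer that baseline is contaminated too, because adolescents enrolled antenatally during baseline may deliver after the training. With waves set by interview date, such an adolescent is interviewed after delivery, hence after training, and falls correctly in endline. An interview held before the training can only concern a birth before it.
- A reader might assume a 30-day endline and obtain 7/30 = 23%. No such fill time is stated, and the article plans three months.
- A reader might conclude that the arms are observed in different calendar periods and that the DID fails. The article gives no workshop calendar and does not say that training dates differ between districts; a common window is an equally natural reading. What stands is that the control cut-off is not stated.

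**What to change.** Assign the wave by date of delivery, not by date of interview.
- Baseline: births before training starts at that intervention facility.
- Endline: adolescents admitted for delivery after training is completed at that facility.
- Keep out of endline any birth during the training days and any birth before training that is interviewed afterwards.
- Apply the three-month endline window to births, and let interviews run up to 14 days beyond it, so that the last births still get the full two-week interval.
- Give each control facility the same calendar cut-off as its matched intervention facility.
- State that only births meeting the endline definition count towards the endline target, and align the entry routes in Inclusion criteria and Sampling procedure with it.

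The cost is wording, use of a delivery date that the two-week rule already needs, and at most a two-week shift in the endline window. The change should be made before endline opens, because enrolment under the wrong boundary cannot be repeated.

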### Data processing and statistical analysis

Both baseline and endline data will be reviewed and edited for completeness and consistency daily. The primary outcome variable of interest is defined as disrespectful intrapartum care which is measured as a response of “Yes” to any of the nine mistreatment questions. The explanatory variables of interest include socio-economic status, educational level, marital status and knowledge of health rights. Data will be collected on the KoBoCollect platform, synced onto a web server and downloaded in Ms-Excel format to the principal investigator’s computer. The data will be exported in STATA version 16 for cleaning and analyses. Descriptive statistics as well as binary and multiple logistic regressions will be computed. Additionally, Difference in Differences (DID) will be calculated to determine the net RMC training intervention effect on mistreatment and RMC. Finally, statistical significance of the RMC training intervention effect will be evaluated using adjusted prevalence ratio, adjusted odds/risk ratio at 95% confidence interval (CI) and *P*-Value of less than 0.05.

Audiotapes from qualitative interviews will be translated and transcribed verbatim into Ms-Word format in English. Themes will be identified and coded in Ms-Excel and exported into NVivo for analyses. Quotes will be narrated and cited in participant codes.

Data analysis for qualitative and quantitative data will be conducted separately. Subsequently, inferences from both qualitative and quantitative results will be jointly used to draw conclusions.

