**Methods:**

This study will employ a pre-test post-test quasi-experimental design. At pre-test and post-test, quantitative surveys will be conducted among adolescents who deliver at health facilities about their labour experience with mistreatment and RMC. A total target of 392 participants will be recruited across intervention and control facilities. Qualitative interviews will also be conducted with selected adolescents and health professionals for an in-depth understanding of the phenomenon. Following the pre-test, a facility-based training module will be implemented at intervention facilities for the facility midwives. The modules will be co-facilitated by the principal investigator and key resource persons from the district health directorate Quality of Care teams. Training will cover the rights of adolescents to quality healthcare, classifications of mistreatment, RMC as a concept and the role of professionals in providing RMC. No intervention will occur in the control facilities. Descriptive statistics, logistic regressions and difference in differences analyses will be computed. Qualitative data will be transcribed and thematically analysed.

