## Methods

### Study settings

The study intervention will be sited in three regions in Ghana: Eastern, Central and Greater-Accra regions. The intervention sites are public health facilities in the Lower Manya Krobo, Upper Manya Krobo district, and the Awutu-Senya East Municipality. The control sites will be in the Ada East, Shai-Osudoku and Effutu Districts. These districts have an average of 11% of their population being adolescent females [42] and reported adolescent pregnancy rates higher than the national average of 14% [22] . The intervention and control sites are selected health facilities which are matched on the type of facilities being district health centres and district hospitals. For each of the intervention sites, a senior member of the district quality of care team will be included as a resource person in the RMC trainings.

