### Sample size determination

The minimum sample size for adolescents is obtained observing the assumptions that the estimated proportion of women who encounter mistreatment during childbirth is 18% [43] and the proposed intervention may reduce this by 10 percentage points. Additionally, a 5% margin of error, a 95% significance level and 80% power are estimated.
N = estimated sample size for one arm.Za = Critical value at confidence interval of 95% (1.96).Zb = Critical value at power of 80% (0.842).d = Actual difference in proportion between control and intervention groups (0.1).P = Average of difference in proportion of both groups

$$ \mathrm{N}=2\times \frac{{\left( Z\alpha + Z\beta \right)}^2}{d^2}\times p\left(1-p\right) $$

An intra-cluster design effect of 1.11 and a non-response adjustment of 10% is factored to obtain a minimum sample size of 392.

A minimum of 10 healthcare participants and 10 adolescents will be included in qualitative Key Informant Interviews It is anticipated that the number of interviews will allow a sample size large enough to allow data saturation to understand the phenomenon of mistreatment from both provider and client perspectives.

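### The test of the training effect names only individual-level methods, although training is allocated three districts against three and the sample size assumes clustering

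*Protocol article*

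**What the plan says.** All references are to the protocol article.

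- **Allocation.** Under Study settings: "The intervention sites are public health facilities in the Lower Manya Krobo, Upper Manya Krobo district, and the Awutu-Senya East Municipality". Then: "The control sites will be in the Ada East, Shai-Osudoku and Effutu Districts". A woman's district therefore fixes her arm. Sampling procedure says the choice was not random: "six districts were purposefully selected from these regions considering appropriateness for the intervention, available resources, and geographical non-proximity".
- **Delivery.** The Methods part of the abstract says that "a facility-based training module will be implemented at intervention facilities for the facility midwives". The outcome is recorded for each adolescent.
- **Clustering at the design stage.** Sample size determination applies "An intra-cluster design effect of 1.11".
- **Analysis.** Under Data processing and statistical analysis: "Descriptive statistics as well as binary and multiple logistic regressions will be computed". DID is then named for the net effect of the training, and the rule for significance follows: "statistical significance of the RMC training intervention effect will be evaluated using adjusted prevalence ratio, adjusted odds/risk ratio at 95% confidence interval (CI"), with P below 0.05. The explanatory variables listed (socio-economic status, education, marital status, knowledge of rights) all belong to the individual woman. No random effect, estimating equation, robust variance, cluster-level comparison or small-cluster correction is mentioned.

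**The concern.** The sample size section accepts that women in the same cluster resemble one another. The analysis section names models, effect measures and a threshold, and as written these treat each woman as an independent observation. The training effect is in fact learned from how three districts changed compared with how three others changed.

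If staffing, management or season moves one district between waves for reasons unrelated to training, the individual-level standard error leaves that movement out. The error runs towards declaring an effect that is not there. Effectiveness of the training is the overall aim, and the results are meant to inform policy, so this test is the one that matters most.

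**Working it through.** **1. The plan's own sample size.** Inputs from Sample size determination: 18% falling by 10 points to 8%, z-values 1.96 and 0.842, d = 0.1. I take p as the mean of the two proportions, 0.13.

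- N = 2 × (1.96 + 0.842)² / 0.1² × 0.13 × 0.87 = 177.6, so 178 per arm and 356 in total.
- With both stated adjustments: 356 × 1.11 × 1.10 = 435, or 356 × 1.11 / 0.9 = 439. Neither is 392.
- With non-response alone: 356 × 1.10 = 391.6, which rounds up to 392. With the design effect alone: 356 × 1.11 = 395.

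The stated total is best matched without the design effect. That is a separate matter, but it means the 392 cannot be relied on to have absorbed the clustering.

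**2. The ICC implied by 1.11.** ICC = (1.11 − 1)/(m − 1).

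- 392/6 = 65.3 women per district: 0.11/64.3 = 0.0017.
- If the 392 covers both waves, 32.7 per district per wave: 0.11/31.7 = 0.0035.

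**3. False-positive rate of the individual-level test.** If the true variance of the contrast is DE times the one used, the rate is 2 × [1 − Φ(1.96/√DE)].

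- DE = 1.11: 1.96/1.054 = 1.860, giving 6.3%.

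For a DID, only district-by-period variation inflates the variance, so DE = 1 + (m − 1) × ICC, using the district-by-period ICC. The documents give no ICC; the values below are assumptions. The article does not make clear whether 392 is the total over both waves (about 33 per district per wave) or the number per wave (about 65, some 784 women in all), so both are shown.

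| Assumed district-by-period ICC | DE, m = 33 | Rate | DE, m = 65 | Rate |
|---|---|---|---|---|
| 0 | 1.00 | 5% | 1.00 | 5% |
| 0.01 | 1.32 | 9% | 1.64 | 13% |
| 0.02 | 1.64 | 13% | 2.28 | 19% |
| 0.05 | 2.60 | 22% | 4.20 | 34% |

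Simulation of the arm-by-period logistic test (six districts, two waves, 18% prevalence, 20,000 runs per setting) agrees to within about a percentage point.

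**4. How much depends on stability over time.** Take a total district ICC of 0.05 and 33 women per district per wave. If 20%, 50% or 100% of the district variance is specific to the period, DE is 1 + 32 × 0.05 × share = 1.32, 1.80 or 2.60, and the rate is about 9%, 14% or 22%. If all of it is constant over time, the rate stays near 5%.

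**5. Six districts.** Comparing three changes with three leaves 6 − 2 = 4 df and a critical value of 2.776. Using 1.96 on 4 df gives P(|t| > 1.96) = 12.2%, so large-sample cluster-robust errors do not cure the problem. In simulation the 4-df t-test on the six district changes held about 5% in every setting. At DE = 1.11 its interval is (2.776/1.96) × √1.11 = 1.49 times the individual-level width.

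**6. Power of the 4-df test for 18% to 8%, no district-by-period variation.** SE of the DID = √[(3 × 0.18 × 0.82 + 0.08 × 0.92)/n], with n women per arm per wave.

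- n = 98 (about 33 per district per wave): SE = 0.0726, power 18 to 19%.
- n = 196 (about 65 per district per wave): SE = 0.0513, power 32%.

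**The case against.** The strongest reply is that a reader might infer that the study will ignore clustering, and the article does not say so. It is a condensed account, nothing in it rules out robust or multilevel versions of the named models, and the design effect shows the authors knew of the issue. This stands. What the text supports is that the stated rule does not account for clustering. It is still more than missing detail, because the section fixes models, measures and threshold in terms that do not fit the sample size section, and the usual later addition of robust errors would not work with six districts.

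A second inference would be that the intervals are certainly too narrow. The documents do not support that either. DID removes district differences that are constant over time, and then the individual-level test holds about 5%. The inflation needs district-specific change between waves, which the article does not quantify, and on its own figure of 1.11 the inflation is small. Against this, the Limitations section credits DID with handling observed and unobserved confounders. That is true only of those that do not change between waves.

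A third inference would be that leaving the facility matching out of the analysis is an error. It is not one in itself.

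Finally, facilities are more numerous than districts if districts contribute several each, so clustering by facility might seem to leave more degrees of freedom. The article does not give the number of facilities, and arm is fixed by district, so a facility-level analysis would still miss changes shared across a district.

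**Conclusion.** The point holds in conditional form. The rule for the training effect names only individual-level methods, while the design has six allocated districts and an assumed design effect of 1.11.

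The false-positive rate is about 5% if district effects are constant over time and 6.3% if the contrast carries the plan's own design effect. At 33 women per district per wave it is about 9%, 13% and 22% for assumed district-by-period ICCs of 0.01, 0.02 and 0.05. It is higher if each wave has 392 women. The figures rest on equal numbers per district and a prevalence of 18%. The direction, towards a false claim of benefit or harm, does not depend on the ICC chosen as long as it is above zero.

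**What to change.** In Data processing and statistical analysis, state that the primary test of the training effect will be one of these:

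- a comparison between arms of the six districts' endline-minus-baseline changes in the proportion mistreated, using a t distribution on 4 df; or
- an individual-level DID model with cluster and period effects, in which the standard error reflects variation between clusters in their change over time and the degrees of freedom are small-sample ones based on the number of clusters.

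Do not rely on large-sample cluster-robust errors. Use the unclustered logistic models only for descriptive risk-factor work, and make no claim about the training effect from them.

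The text change is one paragraph and the programming is light. The real cost is precision: intervals about one and a half times as wide at the plan's own design effect, and power of about 18% (33 women per district per wave) or 32% (65) for the 10-point effect, even with no district-by-period variation. That low power follows from having six districts and should be stated alongside the 80% in Sample size determination.
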